## Abstract

**Introduction:**

People with severe mental illness (SMI) die on average 10–20 years earlier than the general population. Most of these deaths are due to physical health conditions. The aim of this cross-sectional study is to determine the prevalence of physical health conditions and their associations with health-risk behaviours, health-related quality of life and various demographic, behavioural, cognitive, psychological and social variables in people with SMI attending specialist mental health facilities in South Asia.

**Methods and analysis:**

We will conduct a survey of patients with SMI attending specialist mental health facilities in Bangladesh, India and Pakistan (n=4500). Diagnosis of SMI will be confirmed using the Mini-international neuropsychiatric interview V.6.0. We will collect information about physical health and related health-risk behaviours (WHO STEPwise approach to Surveillance (STEPS)); severity of common mental disorders (Patient Health Questionnaire-9 (PHQ-9) and General Anxiety Disorder scale (GAD-7)) and health-related quality of life (EQ-5D-5L). We will measure blood pressure, height, weight and waist circumference according to WHO guidelines. We will also measure glycated haemoglobin, lipid profile, thyroid function, liver function, creatinine and haemoglobin. Prevalence rates of physical health conditions and health-risk behaviours will be presented and compared with the WHO STEPS survey findings in the general population. Regression analyses will explore the association between health-risk behaviours, mental and physical health conditions.

**Ethics and dissemination:**

The study has been approved by the ethics committees of the Department of Health Sciences University of York (UK), Centre for Injury Prevention and Rehabilitation (Bangladesh), Health Ministry Screening Committee and Indian Council of Medical Research (India) and National Bioethics Committee (Pakistan). Findings will be disseminated in peer-reviewed articles, in local and international conferences and as reports for policymakers and stakeholders in the countries involved.

**Trial registration number:**

ISRCTN88485933; 3 June 2019.

Strengths and limitations of this studyThe study uses standardised tools to measure patient outcomes that will allow us to compare the findings with those of the general population.The survey will be conducted face to face by trained researchers.The questionnaire has been translated into the most common languages used in Bangladesh, India and Pakistan using validated translations of standardised measures where available.The survey is being conducted in specialist centres and is therefore a healthcare utilisation sample drawn largely from tertiary care.The study population may not be representative of all the people with severe mental illness in each country, as those not accessing specialist centres are not included in the survey.

## Background

A considerable body of research has shown that people with severe mental illness (SMI; that is, psychotic disorders, bipolar affective disorder and severe depression with psychotic symptoms) die on average 10–20 years earlier than the general population.^1 2^ Around 80% of deaths in people with SMI are due to preventable physical illnesses, most commonly cardiometabolic diseases, respiratory disorders and infectious diseases.^3 4^This excess mortality is a major global public health challenge but efforts to address it have been limited. Recent studies suggest that despite an overall improvement in life expectancy for both the general population and people with SMI, the absolute mortality gap between these two groups is actually widening.^5–7^

Prevalence of most physical health conditions is higher and outcomes are poorer in this population.^8^ Multimorbidity (the presence of two or more conditions) is also more common^9^ in the presence of SMI, contributing to poorer physical health and quality of life. The majority of evidence for these health inequalities has been generated in high-income countries (HICs), but a small number of studies from low-income and middle-income countries (LMICs) also show a similar pattern of increased mortality for people with SMI, with an even shorter life expectancy, and larger mortality gap.^4 10–12^ The few studies available suggest that physical comorbidity in SMI is at least as prevalent as in developed countries.^1^

In South Asia, rates of mental illness and physical non-communicable diseases have been increasing rapidly.^13 14^ This increase, coupled with the lack of access to even basic mental healthcare,^15^ and neglect of the physical health needs of people with SMI by policymakers and healthcare services,^16^ means that the burden of disease due to physical disorders in people with mental illness. is set to rise further, with a corresponding increase within country and global health inequalities. This increase is coupled with a recognised lack of information about the prevalence of physical conditions and health risk behaviours in the SMI population in South Asia.^17^ This gap in knowledge, particularly in relation to health service planning in LMICs, has been pointed out repeatedly as a priority for research.^18^ Addressing mental and physical health comorbidity in LMICs is also a global priority, recognised in global policies to help achieve the sustainable development goals, including ‘ensuring healthy lives and promoting well-being for all’.^19–21^ A detailed understanding of the prevalence of physical health conditions, health risk behaviours and health service utilisation in SMI in LMICs is needed to progress this agenda.^22^

### Objectives

In people with SMI attending specialist mental health facilities:

Determine the prevalence of physical health conditions (ie, type 2 diabetes, hypertension, heart disease, obesity and infectious diseases) and health-risk behaviours (ie, diet, physical activity, alcohol and tobacco use) and compare these findings with those reported in the general population.Determine the association between physical health conditions, health-risk behaviours, health-related quality of life and various demographic, behavioural, cognitive, psychological and social variables.Identify health-service utilisation and the type of lifestyle advice that has been offered for this population.Support clinical trial readiness by providing evidence-based findings regarding outcome measures and procedures relevant for clinical trial design.

## Methods and analysis

### Design, settings and population

We will conduct a cross-sectional survey among patients with a clinical diagnosis of SMI recruited at national specialist mental health institutions. In Bangladesh, the study will be conducted at the National Institute of Mental Health and Hospital (NIMHH) in Dhaka. NIMHH offers 200 beds for in-patient care and on average 400 outpatients attend every day. In India, the study will be conducted at the National Institute of Mental Health and Neurosciences (NIMHANS) in Bengaluru, with 650 beds for in-patient care; on average at NIMHANS, 400 outpatients attend every day. In Pakistan, the study will be conducted at the Institute of Psychiatry (IOP) Rawalpindi Medical University, a WHO collaborating centre for the Eastern Mediterranean. IOP offers 60 beds for inpatients and on average 400 outpatients attend every day. All three national institutes serve patients from all over the country. Adults (18 years and over) with a clinical diagnosis of SMI (defined by the International Classification of Disease 10th revision (ICD-10^23^) as schizophrenia, schizotypal and delusional disorders (F20-F29); bipolar affective disorder (F30, F31) and severe depression with psychotic symptoms (F32.3, F33.3)),^23^ who are able to provide informed consent as assessed by the treating clinician will be recruited. Patients who lack capacity to provide consent or are unable to complete study questionnaires will be excluded (figure 1). The data will be collected from June 2019 to September 2020.

**Figure 1 F1:**

Study flowchart.

### Sample size

We aim to build as large a sample as possible within the resources available over the study period (n=1500 per country). As an indicative example of survey precision to address some of the key research questions, we provide a sample size estimate for investigating the prevalence of diabetes. Assuming a prevalence estimate of 10% (based on results from previous studies,^24^ we will need 857 participants per country to achieve ±2% precision assuming a 95% CI.^25^

### Recruitment and random selection of the participants

Both inpatients and outpatients attending one of the three specialist mental health institutions collaborating in this study will be recruited. At NIMHH and NIMHANS, patients will be selected randomly using random number tables generated centrally to determine for outpatients, which patient to approach on a given day, and for inpatients by randomly selecting beds. Recruitment is separated by inpatients versus outpatients, resulting in a proportion of 80% outpatients and 20% inpatients (which has been reported as the ‘usual’ proportion of inpatients and outpatients). Due to the lower volume of patients and outpatients reaching the centre outside working hours at the IOP, all patients attending the IOP during the study duration will be invited to participate in the survey.

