### Statistical analysis

Quantitative data will be summarised using descriptive statistics. First, prevalence rates of infectious diseases, long-term physical health conditions (eg, diabetes, heart disease) and health-risk behaviours for type II diabetes, cardiovascular and respiratory disorders (eg, tobacco use, obesity, physical activity, diet) will be estimated in the SMI population. Second, we will examine the associations between physical health conditions and health-risk behaviours, using regression models with random intercepts for data collection site with the following potential covariates: demographic variables (ie, age, sex and level of education), history of mental and physical conditions and biomarkers (eg, body mass index, BP). These regression models will also be used to calculate prevalence rates of physical health conditions and health-risk behaviours adjusted for these covariates (eg, for comparison with external general population data). Further regression analyses will explore the association between mental and physical health conditions and health-related quality of life measured using EQ-5D-5L. Regression models will take account of the nature and distribution of data (eg, count vs continuous data; skewed vs normally distributed data). To investigate the prevalence of physical health conditions and health risk behaviours in the general population, we will extract aggregated data on the prevalence of physical health conditions, health risk behaviours and lifestyle advice from the last available WHO STEPS survey from Bangladesh,^44^ India^45^ and Pakistan.^46^

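### Two sites recruit to one common 80/20 outpatient/inpatient split and the third invites all attenders, but care setting is not a listed covariate, so prevalences and associations may partly reflect setting

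*Protocol article*

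**What the plan says.** **Recruitment.** Under Recruitment and random selection of the participants, the protocol article states: "At NIMHH and NIMHANS, patients will be selected randomly using random number tables generated centrally". Outpatients are drawn by day and inpatients by bed. It continues: "Recruitment is separated by inpatients versus outpatients, resulting in a proportion of 80% outpatients and 20% inpatients". The same sentence adds in brackets that this mix has been reported as the usual one. It gives one figure for both sites and no breakdown by site. The third site works differently: "all patients attending the IOP during the study duration will be invited to participate in the survey".

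**Site size.** Under Design, settings and population: "NIMHH offers 200 beds for in-patient care and on average 400 outpatients attend every day". NIMHANS is described as "with 650 beds for in-patient care; on average at NIMHANS, 400 outpatients attend every day". IOP has 60 beds and also about 400 outpatients a day. There is one institute per country.

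**Analysis.** Under Statistical analysis, prevalences are estimated first. Associations are then examined "using regression models with random intercepts for data collection site with the following potential covariates". The list names age, sex, education, history of mental and physical conditions, and biomarkers. Care setting is not on it. The same models also supply adjusted prevalences, for example for comparison with external general population data.

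**The concern.** Setting is the variable on which two of the three samples are stratified, and inpatients and outpatients with SMI may well differ in tobacco use, activity, weight and treatment. Three results could be affected.

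- **Overall prevalence at a quota site.** It is an average over a mix fixed in advance. If the institute's SMI patients are not 20% inpatients and the condition differs by setting, the average moves away from that of the attending population.
- **Differences between sites.** Two sites have a fixed mix and the third has whatever arrives. Because each site stands for a country, setting and country may be partly mixed.
- **Associations.** If setting relates to both a behaviour and a condition, leaving it out can confound their association. This holds even if 80/20 is exactly right, because proportional allocation protects the overall prevalence and not a regression coefficient. The random intercept for site absorbs differences in level between sites, not differences between inpatients and outpatients within one.

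**Working it through.** **1. The plan's own precision figure.** Inputs from Sample size: prevalence 10%, precision ±2 points, 95% confidence, 857 per country needed, 1500 per country planned.

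n = 1.96² x 0.10 x 0.90 / 0.02² = 864.3, so 865. The stated 857 is within 1% of this, and a finite population correction with an assumed N of 100,000 gives 857.0. The figure reproduces.

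Half-width at n = 1500: 1.96 x √(0.09/1500) = 1.52 points.

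**2. Does one split look plausible at both quota sites?** Inputs from Design, settings and population.

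| Site | Beds | Outpatients per day | Beds / (beds + one day's outpatients) |
|---|---|---|---|
| NIMHH | 200 | 400 | 200/600 = 33% |
| NIMHANS | 650 | 400 | 650/1050 = 62% |
| IOP (no split) | 60 | 400 | 60/460 = 13% |

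Beds per daily outpatient are 0.50 at NIMHH and 1.625 at NIMHANS, a ratio of 3.25. For 20% to be right at both, length of stay, repeat visits and the SMI fraction would have to offset that ratio. These are one-day snapshots of all patients, so they raise doubt and do not measure W.

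**3. Size of the shift.** With a sample fixed at 20% inpatients:

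shift = (0.20 - W) x (p_in - p_out)

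The article gives neither W nor the difference, so both are assumptions. For differences of +10 and +5 points (the sign reverses if prevalence is lower in inpatients):

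| Assumed W | Shift, 10-point difference | Shift, 5-point difference |
|---|---|---|
| 5% | +1.5 | +0.75 |
| 13% | +0.7 | +0.35 |
| 20% | 0 | 0 |
| 33% | -1.3 | -0.65 |
| 62% | -4.2 | -2.1 |

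If the settings do not differ, the shift is zero at every W.

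**4. Price of weighting.** Re-weighting a 20/80 sample to W, with about the same variance in both strata:

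design effect = W²/0.20 + (1 - W)²/0.80

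| W | Design effect | Diabetes half-width at n = 1500 |
|---|---|---|
| 5% | 0.0125 + 1.1281 = 1.14 | 1.62 |
| 13% | 0.0845 + 0.9461 = 1.03 | 1.54 |
| 20% | 1.00 | 1.52 |
| 33% | 0.5445 + 0.5611 = 1.11 | 1.60 |
| 62% | 1.9220 + 0.1805 = 2.10 | 2.20 |

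Each half-width is 1.52 x √(design effect).

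**The case against.** The strongest reply is that the article presents 80/20 as the usual mix, which is proportional allocation. If 20% is the true share at a site, the sample there is self-weighting and the shift is zero by the formula above. Inviting everyone at IOP also aims at the natural mix, so the two schemes share an intention. This stands as far as overall prevalence goes. It does not supply a site-specific basis for one figure at two very different institutes, and it does not touch the associations.

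A reader might infer from the 33% and 62% that an 80/20 split cannot be self-weighting. The documents do not support that. Those ratios set a stock of beds against a single day's outpatient flow, cover all diagnoses, and ignore how admissions and visits accumulate from June 2019 to September 2020. For the same reason the 4.2-point value at 62% is an illustration and not an estimate.

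The article also calls its covariates potential, and a fuller protocol or analysis plan may hold weights or a setting term. This stands in part: the absence of weights from a journal article proves nothing. What remains is that the covariate list the article does give leaves out the variable its recruitment is stratified on. Comparison between countries is also not a listed objective, so mixing of setting with country is the lesser consequence.

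**Conclusion.** The concern holds in a limited form. One common split is used at two sites without a site-specific basis, a different scheme is used at the third, and care setting is missing from the listed covariates. Overall prevalences may be shifted, and differences between sites and associations may partly reflect setting.

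The size is unknown from the article. It is nil if W is 20% or if the settings do not differ. For an assumed 10-point difference it is 0.7 to 1.5 points for W of 5%, 13% or 33%, about the size of the 1.52-point half-width at n = 1500 or smaller. It would exceed that half-width clearly only if W were far from 20%, as at 62%. One should not conclude that the quota has biased the prevalences, since that depends on two quantities the article does not give. The case for putting setting in the regressions does not depend on W.

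**What to change.** (a) Add inpatient/outpatient setting as a fixed covariate, alongside site, in the regressions and in the models that produce the adjusted prevalences, and state the setting mix to which those prevalences refer.

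(b) Report each prevalence by site and setting, including IOP.

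(c) From hospital registers, report each institute's unduplicated SMI inpatient share over the study period. Where it departs from the sample's share, give a setting-weighted overall prevalence, with standard errors that allow for the weights, beside the unweighted one.

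The cost is small for (a) and (b). Setting is already used in recruitment at the two quota sites and only has to be recorded at IOP as well. Item (c) needs the register counts and widens the interval of the weighted estimate. The widening is slight for the W values of 5%, 13% and 33% (design effect 1.03 to 1.14, half-width at most 1.62 points). At W = 62% it is not: the design effect is 2.10 and the half-width 2.20 points, beyond the ±2 used as the article's example. The shares should therefore be obtained before the weighted figure is given prominence.

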### Informed consent

In the first instance, the researchers will give an information sheet to the patient, providing written and verbal information on the potential benefits and risks of taking part in the study and clarifying the assessments involved in the study. Only people who provided written informed consent will be included in the study. Where there are problems with literacy, the researchers will provide this information verbally to both the carer and the patient. Those unable to provide a signature will be requested to indicate their consent with a thumbprint. The information sheet will meet all the requirements of the relevant ethics committees. Maintenance of confidentiality and compliance with international, UK and relevant local Data Protection Acts will be emphasised to all study participants. Moreover, all participants will be informed that their participation in the study is voluntary, consent can be withdrawn at any stage and the decision about participation will not affect their care.

Mental capacity is time specific and decision specific. For patients who are assessed to lack capacity by their local physician, seeking informed consent will be delayed until capacity is regained, if feasible. No assessments will be continued where the patient appears reluctant, even where patient consent has been obtained.

Optional ‘consent to contact’ about future studies will be sought from survey participants. Permission will be sought to retain participant details and to contact participants about future studies that may be relevant for them. Again, it will be emphasised that this is voluntary, they can withdraw permission at any time and this will not affect their care in any way. After consenting to participate, the participant will be given a unique patient identifier (ID) by the researcher. The patient consent and contact information will be entered into a database (participant log), which will be kept separate from the survey result database. The survey result database will include only the unique patient ID and no patient identifiable data.

### Confirmation of eligibility

SMI diagnosis will be confirmed by trained researchers using the relevant modules from the Mini-International Neuropsychiatric Interview (MINI) V.6.0.^26^ The MINI is a short diagnostic structured interview to explore mental disorders. It is designed to allow administration by non-specialist interviewers.^27^ The inter-rater reliability for the MINI will be assessed at each site at the start of the study. Within each study site, at least 10 MINI questionnaires will be completed and compared between two different researchers blinded from each other. Where needed, further training will be offered to achieve acceptable inter-rater reliability before researchers are assigned to the study.

### Data collection

We will conduct a face-to-face digital survey to collect information about physical health and health-risk behaviours, severity of common mental disorders and health-related quality of life using validated instruments as described below. The survey has been translated into the most common languages in the countries (Urdu in Pakistan, Bangla in Bangladesh and Hindi, Kannada, Tamil and Telugu in India). The team of interviewers in each county will include men and women and will include researchers who speak regional dialects, which is consistent with usual clinical practice in these settings.^28^ Participants will be able to express a preference to be interviewed by a researcher of the same gender, to reduce response bias that might arise due to the gender of the interviewer.

The WHO STEPwise approach to Surveillance (STEPS) instrument V. 3.2 will be used to collect information about non-communicable diseases and related health-risk behaviours.^29^ STEPS is an international standardised tool that will allow comparisons with the general population within the country and between countries.^30^ The instrument has already been translated, used and validated in the general population in Bangladesh, India and Pakistan.^31–33^

To allow patients to disclose information on sexually transmitted diseases, HIV diagnosis, alcohol and tobacco consumption, in agreement with patient’s wishes, the interviewer will ask the caregivers/attendants to leave the room for this part of the interview.

#### Demographic information

The STEPS demographic module will be used to collect information on age, sex, education, marital status, employment, household assets and income.^29^

#### Mental health

We will collect information relevant to the SMI diagnosis of each participant, including duration of the mental illness, any treatment or medication and duration of the treatment and/or medication. The 9-item depression module (Patient Health Questionnaire-9 (PHQ-9))^34^ will be used to measure the severity of depressive symptoms and the generalised anxiety disorder 7-item scale (GAD-7)^35^ for the severity of anxiety symptoms.

